#### 4. Main study parameter (endpoint)

##### Response to treatment

##### a. At 6 month follow-up:

Criteria for complete uveitis resolution applied to both eyes, in cases with bilateral uveitis, included: (1) fewer than or equal to 0.5+ anterior chamber cells according to the Standardized Uveitis Nomenclature (SUN) grading system, fewer than or equal to 0.5+ vitreous haze based on clinical grading using the NEI (National Eye Institute) scale, and no

active retinal or choroidal lesions; and (2) no more than 7.5 mg of oral prednisone daily (i.e., methylprednisolone at 6 mg or less daily) and fewer than or equal to 2 drops of prednisolone acetate 1% (or equivalent) per day. Treatment will be categorized as a failure if subject did not meet the following criteria at the 6-month follow-up.

Type of data: Categorical

## **5. Additional study parameters (endpoints)**

- a. Time to uveitis resolution: Calculated from the time of randomization.

Type of data: time (in months)

- b. Uveitis relapse (subsequent follow-up, beyond 6 months)

Relapse: any worsening of ocular inflammation (including a two-step increase in anterior chamber or vitreous cells as per the SUN grading system) or the occurrence of clinically new inflammatory activity (such as choroidal or retinal lesions) that necessitated a modification of local or systemic uveitis treatment after a minimum of 90 days of complete uveitis resolution at the patient level.

Type of data: Categorical

- c. Time to relapse was calculated from the first visit showing inactive uveitis until the first notification of uveitis relapse.

Type of data: time (in months)

### Ocular-level outcomes

- d. Secondary glaucoma: the occurrence of increased intraocular pressure (IOP) above 21 mmHg in at least two consecutive visits that necessitated prescription of IOP-lowering medications.

Type of data: Categorical

- e. Visual acuity: Visual acuity was considered to increase if the difference in best-corrected visual acuity between month 6 and baseline visits (measured with Snellen, in decimal equivalent) was equal to or greater than 0.1, stable if within the range of -0.1 to 0.1, and decreased if less than -0.1.

(If any cataract or vitreoretinal surgery was performed before the six-month follow-up, the last recorded visual acuity prior to the surgery was used).

Type of data: Categorical

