### ***Secondary objectives***

- a) To explore details of treatment details of treatment failure (partial resolution or non-responsive), time to uveitis resolution, uveitis relapse following complete resolution, and eye-level outcomes, which consisted of the differences in visual acuity between baseline and month 6, as well as the incidence of secondary glaucoma.
- b) To explore relevant biomarkers at baseline, during, and at the end of primary end point (6 months follow-up).

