## **6. Other baseline variables**

- xxvi. Age (numerical data)
- xxvii. Laterality of ocular inflammation (categorical data): unilateral or bilateral
- xxviii. Sex (categorical data): male or female
- xxix. Onset (numerical data): days of ocular complaints
- xxx. Chronicity (categorical data): acute or chronic
- xxxi. Previous TB (categorical data): yes or no
- xxxii. Contact TB history (categorical data): yes or no
- xxxiii. Baseline visual acuity (numerical data): Snellen/LogMAR visual acuity, and categorical data: mild visual impairment, moderate visual impairment, severe visual impairment, and blindness.
- xxxiv. IOP (numerical and categorical data): increased or not
- xxxv. Keratic precipitates (categorical data): mutton-fat, fine, or others
- xxxvi. Anterior chamber cells (numerical data)
- xxxvii. The presence of iris nodule (categorical data): yes or no
- xxxviii. Scleral involvement (categorical data): yes or no
- xxxix. Synechia formation (categorical data): yes or no
  - xl. Lens status (categorical data): cataract, pseudophakia, phakic)
  - xli. Vitreous haziness (categorical data): yes or no
  - xl.ii. Vitreous cells (numerical data)
  - xl.iii. Snowball/snowbank (categorical data): yes or no
  - xliv. Retinal vascular changes (categorical data): yes or no
  - xl. v. Optic nerve involvement (categorical data): yes or no
  - xlvi. Retinitis or retinal infiltrates (categorical data): yes or no
  - xl. vii. Choroiditis (categorical data): yes or no
  - xl. viii. Posterior granuloma/tuberculoma appearance (categorical data): yes or no
  - xl. ix. Retinal detachment (categorical data): yes or no
    - l. Macular edema (categorical data): yes or no

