## **7. Sample size calculation**

The sample size is calculated using a formula of two-independent proportion sample size calculation. The primary end point of uveitis resolution at 6 month is used for this sample size calculation.

Based on the Multicenter Uveitis Steroid Treatment (MUST) trial in non-infectious uveitis, the proportion of uveitis patients with active disease at six months following treatment was found to be 44%. A 30% difference in uveitis resolution between the two groups is predetermined. Using a  $Z\alpha$  of 1.96 and a  $Z\beta$  of 0.84 (for a two-sided significance level of 5% and 80% power), the estimated sample size required for each treatment group will be 35 participants. With 10% increase to anticipate dropout, a total of 39-40 participants in each treatment group is required.

$$N1 = N2 = \left( \frac{Z\alpha\sqrt{2PQ} + Z\beta\sqrt{P1Q1 + P2Q2}}{P1 - P2} \right)^2$$

$Z\alpha$  (1.96), power (80%,  $Z\beta = 0.84$ ),  $P1$  based on MUST trial 44% ( $Q2 = 56\%$ ). Estimated  $P1 - P2 = 30\%$ . Thus,  $P2 = 14\%$  ( $Q2 = 86\%$ ). As 10% drop out rate is being anticipated,  $N1 = N2 = 39 \sim 40$  (total 78-80 participants)

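### Visual acuity change is reduced to three classes with no numeric or baseline-adjusted comparison, so this secondary outcome gives no size of difference and usually loses power

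*Supplement*

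**What the plan says.** Protocol version 2.0, section 1.2, lists among the secondary objectives, under exploratory wording, "the differences in visual acuity between baseline and month 6". SAP version 2.0, section 6, records "Baseline visual acuity (numerical data): Snellen/LogMAR visual acuity", so acuity exists as a number at baseline.

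The outcome itself is defined in SAP section 5, item e, with the same rule in protocol section 6.2, item f: "Visual acuity was considered to increase if the difference in best-corrected visual acuity between month 6 and baseline visits", in decimal Snellen, is at least 0.1. Changes between -0.1 and 0.1 are stable and those below -0.1 are decreased. The SAP gives the data type as categorical.

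SAP section 14 adds little. Item d confines the chi-square or Fisher test to uveitis resolution at six months. Item h says only that involved eyes are counted and that a bilateral case contributes two. No test, model, covariate, mean difference or confidence interval is named for acuity.

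**The concern.** The objective concerns a difference in acuity. The plan computes that difference for each eye, then keeps only which of three bands it falls in. Two things follow.

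First, a table of proportions increased, stable and decreased does not say by how much vision differs between the arms. A gain of 0.1 and a gain of 0.6 count the same. This follows from the text and needs no simulation.

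Second, banding a numeric change usually costs power, and the trial has about 40 participants per arm, a number chosen for a different endpoint. Subtracting baseline is also not the same as adjusting for it: decimal acuity is bounded, so an eye that starts near normal has little room to improve and one that starts very low has little room to worsen. With no stratification and small arms, a chance imbalance in baseline acuity would pass into the classes.

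**Working it through.** **1. The plan's own sample size.** Inputs from SAP section 7: "for a two-sided significance level of 5% and 80% power"; "the proportion of uveitis patients with active disease at six months following treatment was found to be 44" per cent; "A 30% difference in uveitis resolution between the two groups is predetermined". So P1 = 0.44, P2 = 0.14, mean P = 0.29, Q = 0.71.

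n = [(1.96 × √(2 × 0.29 × 0.71) + 0.84 × √(0.44 × 0.56 + 0.14 × 0.86)) / 0.30]² = 34.67, rounded up to 35.

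This agrees with "the estimated sample size required for each treatment group will be 35 participants". Dropout: 35 / 0.9 = 38.9, rounded up to 39, which agrees with "With 10% increase to anticipate dropout, a total of 39-40 participants in each treatment group is required". The figure reproduces, but it concerns resolution. The documents contain no corresponding calculation for acuity.

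**2. Illustration for acuity.** Every input here except the arm size and the cut points is an assumption: 40 per arm, one value per patient, normally distributed change, control mean gain 0.1, SD 0.2, 0.3 or 0.4, and a shift chosen so that a numeric test has 80% power. The normal approximation gives (1.96 + 0.84) × √(2/40) = 0.626 SD. The t distribution on 78 degrees of freedom needs 0.634 SD, at which power is 80.0%.

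Class probabilities at the SAP cuts:
- Increased: control 0.500; ATT Φ(0.634) = 0.737, at any SD.
- Decreased: control Φ(-0.2/SD); ATT Φ(-0.2/SD - 0.634).

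| SD | Control: decreased / stable / increased | ATT: decreased / stable / increased |
|---|---|---|
| 0.2 | 0.159 / 0.341 / 0.500 | 0.051 / 0.212 / 0.737 |
| 0.3 | 0.252 / 0.248 / 0.500 | 0.097 / 0.166 / 0.737 |
| 0.4 | 0.309 / 0.191 / 0.500 | 0.128 / 0.135 / 0.737 |

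For a three-class chi-square the noncentrality is λ = 40 × Σ[(c - m)²/m + (a - m)²/m], where c and a are the control and ATT probabilities of a class and m is their mean. This gives λ = 5.23, 5.23 and 5.18 for the three SDs, and power of about 52% on 2 degrees of freedom.

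Repeated simulations of the same setting gave:
- t-test on the change: 80-82%
- chi-square on three classes: 51-55%
- rank test on the ordered classes: 61-65%

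**3. How far this depends on the assumptions.**
- Control gain varied from 0 to 0.2, effect still set for 80%: loss 21-40 points (chi-square) and 11-28 points (rank test).
- Baseline-adjusted model (ANCOVA) set at about 80%, 35 per arm, baseline to Month 6 correlation 0.3-0.7: chi-square 28-54%, rank test 39-62%, unadjusted t-test on change 57-73%.
- Small effect (0.3 of the Month 6 SD, correlation 0.5, 40 per arm): t-test on change 25%, chi-square 16%, rank test 20%. The loss is 9 and 5 points, and the numeric test is weak too.
- Very large effect (0.8 SD, correlation 0.8, 40 per arm): 100%, 97% and 99%. The loss is 3 and 1 points.
- Bounded acuity with a shift in all eyes: logMAR ANCOVA ahead of the three-class tests by about 13-36 points.
- Bounded acuity where only some eyes respond, with response 30 points apart: t-test on change 38-47%, chi-square 38-48%, rank test on classes 46-55%, logMAR ANCOVA 37-39%, decimal ANCOVA 42-51%. Here the classes lose nothing of note, and the rank test on classes beats logMAR ANCOVA.

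The illustration in step 2 ignores the second eye of bilateral cases and the skew of decimal acuity. Simulation error in the correlation and effect-size grids is about 3-4 points per setting.

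**The case against.** The strongest reply has four parts.

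*No test is named for acuity, so the chi-square and rank tests above are comparators supplied by the review.* This is right, and it is why no power loss can be quoted as a property of the plan. It does not rescue the plan, because the only declared form of the outcome is categorical and no numeric summary is defined anywhere.

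*A numeric model is not always better.* This also stands. A reader might infer that the loss follows from banding as such and would persist at any step size or on any scale. The partial-response scenario contradicts that, so the gain from the numeric model is usual rather than guaranteed.

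*The objective is exploratory, and elsewhere the outcome is called simply visual acuity changes.* The wording is indeed exploratory and lowers the priority. Even an exploratory comparison should report how large the difference is.

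*Proportions improved or worsened are easy to read, and off-chart acuities need no numeric code.* This is a fair advantage, and a reason to keep the table alongside the model.

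**Conclusion.** The point holds in a limited form. From the text alone, the planned acuity outcome yields no estimate of the size of the difference that the objective names, and no baseline-adjusted comparison is planned. In most settings tried it also loses power.

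The amount of loss is not fixed by the documents. Under the assumptions in step 2 of the working it is about 25-29 points for a three-class chi-square and 15-19 points for a rank test. It shrinks for small or very large effects and can disappear if only some eyes respond. A reader might take such a range as what this trial forfeits, or conclude that a moderate real difference in vision would probably be reported as none. The documents support neither. They give no acuity SD, effect, correlation or test, and even in the illustration the categorical tests detect the assumed difference more often than not.

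Acuity is a secondary, eye-level outcome on which the trial was not sized, so the primary result is unaffected. Minor priority.

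**What to change.** In SAP section 5, item e, and section 14, item h, and in protocol section 6.2, item f:

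- Make the main acuity comparison a model of Month 6 acuity in logMAR on arm and baseline logMAR acuity. Report the adjusted mean difference with its 95% confidence interval.
- Account for patients who contribute two eyes, for example with GEE or a mixed model.
- Fix in advance the numeric codes for acuities below the chart.
- Add a rank-based sensitivity analysis, which covers both the choice of codes and the case where only some eyes respond.
- Keep the increased, stable and decreased table as description. As written, a change of exactly 0.1 fits both increased and stable, so state which class it belongs to.

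The cost is wording. Best-corrected acuity is already measured at baseline and Month 6, and these are standard models. The small downsides are that off-chart acuities need an agreed code and that an adjusted mean difference in logMAR is less directly readable than proportions.

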**Study design & study population:****Single blind randomized controlled trial (RCT) – single center**

All newly referred uveitis patients will be evaluated for eligibility at the outpatient uveitis clinic, Department of Ophthalmology, Faculty of Medicine, Universitas Indonesia - Cipto Mangunkusumo Hospital, Jakarta, Indonesia.

Inclusion criteria are: (1) adults (age  $\geq 18$  years) with newly diagnosed, clinically active uveitis of undetermined cause, following standardized workups at our center (see Supplementary file); (2) positive QFT test result ( $>0.35$  U/mL; Kimia Farma Laboratory, Depok, PT. Kimia Farma Diagnostika); (3) local residence in Jakarta, Bogor, Depok, Tangerang, or Bekasi; and (4) consent to participate in the study through the entire monitoring period. Exclusion criteria were: (1) confirmed active systemic TB or living with an active TB patient; (2) HIV-positive status; (3) visual acuity less than hand movement with signs of phthisis on ophthalmological examinations and ultrasound; (4) impaired liver function or other systemic conditions, as assessed by the internist-pulmonologist, that precluded eligibility for ATT; (5) pregnancy, and (6) recent antibiotic use, including ATT, or systemic steroid use exceeding 8 mg prednisone equivalent daily within the last 14 days.

Ocular PCR will be performed in selected cases based on the clinical judgement of the attending uveitis specialist. This will be done (1) to confirm the clinical diagnosis, or (2) to exclude other differential diagnosis. If it is performed, any positive results will result in exclusion from trial entry.

After eligibility assessment, participants will be randomly assigned in a 1:1 ratio to one of the two treatment groups without stratification factors. Randomization will be conducted by a dedicated research manager using block randomization (block size of 4) to ensure equal distribution between the groups.

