## 3. Study population

### a. Population (base)

Patients diagnosed with Uveitis of undetermined cause with positive TB immunoreactivity (IGRA) at the outpatient clinics in [name] National Central Public Hospital, Jakarta.

b. Inclusion criteria:

5. Patient that is newly diagnosed with uveitis of unknown origin/idiopathic (as evidenced by a series of uveitis work-up tests) and tested positive for IGRA ( $>0.35$  U/ml).
6. Age  $>18$  years old.
7. Lives in Jakarta/Bogor/Depok/Tangerang/Bekasi area or willing to participate in research until the end of monitoring program.
8. Willing to participate in the research and sign the informed consent after receiving explanation regarding the research.

c. Exclusion criteria:

13. Patients with positive aqueous tap examination results on one of the examination panels for the bacteria causing infectious uveitis according to the standard examination.
14. Anterior uveitis patient with a positive HLA-B27 test result.
15. The patient is proven to have active TB or lives in the same house with an active TB patient.
16. Patients are included in the TB reactivation risk index group according to the 2018 WHO LTBI (Latent Tuberculosis Incident) Guideline.
17. HIV positive patient.
18. Patients with inactive uveitis at the first visit.
19. Patients with visual acuity less than 1/300 or showing signs of preptisis based on ophthalmological examination and ultrasound of the eye.
20. The patient has a history of previous ATT consumption.
21. Patients with impaired liver function or other systemic conditions which according to the Internal Medicine Department are not eligible to receive ATT.
22. The patient has a history of taking antibiotics in the last 1-2 weeks.
23. The patient is not willing to sign the informed consent.
24. The patient was pregnant at the first visit or was planning to become pregnant during the study period.

d. Sample size calculation

The sample size is calculated using a formula of two-independent proportion sample size calculation. The primary end point of uveitis resolution at 6 month is used for this sample size calculation.

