6.2. Additional study parameters (endpoints)

- a. Time to uveitis resolution: Calculated from the time of randomization. These criteria had to be maintained for at least 90 days following the visit when the first complete uveitis resolution was recorded. If there was insufficient follow-up after resolution, maintained uveitis resolution was still considered. Participants who met criterion 1 but not criterion 2 were classified as having partial uveitis resolution (non-complete uveitis resolution)
- b. Uveitis relapse (subsequent follow-up, beyond 6 months). Uveitis relapse is defined as any worsening of ocular inflammation (including a two-step increase in anterior chamber or vitreous cells as per the SUN grading system) or the occurrence of clinically new inflammatory activity (such as choroidal or retinal lesions) that necessitated a modification of local or systemic uveitis treatment after a minimum of 90 days of complete uveitis resolution at the patient level.
- c. Time to relapse was calculated from the first visit showing inactive uveitis until the first notification of uveitis relapse.

- d. Biomarkers associated with trial from samples obtained from study participants. Exploratory investigations may be conducted as supplementary analyses. Samples will be collected and stored following the institution's standardized procedures for biobanking of human study materials. Details of further analyses will be provided in a separate document.
- e. Secondary glaucoma: the occurrence of increased intraocular pressure (IOP) above 21 mmHg in at least two consecutive visits that necessitated prescription of IOP-lowering medications.
- f. Visual acuity: Visual acuity was considered to increase if the difference in best-corrected visual acuity between month 6 and baseline visits (measured with Snellen, in decimal equivalent) was equal to or greater than 0.1, stable if within the range of -0.1 to 0.1, and decreased if less than -0.1.  
(If any cataract or vitreoretinal surgery was performed before the six-month follow-up, the last recorded visual acuity prior to the surgery was used).

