## **14. Data analysis**

- a. All data will be pseudo-anonymized. A separate dataset (in Excel) containing participant IDs will be protected. A separate dataset without direct participant IDs will be generated and analyzed using SPSS.
- b. Baseline characteristics will be summarized according to trial group for the ITT populations.
- c. The primary outcome analysis will be focused on the proportion of complete uveitis resolution and the corresponding relative risk between the ATT and control groups. Cox proportional-hazards models will be used to estimate any uveitis resolution between the ATT and control groups. This analysis will be performed at the patient level, where resolution of uveitis is considered when both eyes meet the prespecified criteria. In bilateral

uveitis cases, if one eye shows uveitis resolution but the other does not, as prespecified in the previous section, these participants will be considered to have “no uveitis resolution”.

- d. Pairwise comparisons across experimental arms will be done using a Chi-square test or Fisher’s exact test as appropriate at the 5% significance level for the efficacy endpoint of uveitis resolution at six month time point (see above section). Relative risk will be calculated and presented with 95% confidence interval in the ITT and per-protocol analysis approaches.
- e. Time-to-uveitis resolution will be analyzed using the Cox proportional hazards model and hazard ratio.
- f. For uveitis relapse outcomes, the analysis will include participants with complete uveitis resolution, regardless of follow-up duration. Cox proportional hazards models, along with hazard ratio and Kaplan–Meier estimates, will be used for the analysis.
- g. The number (proportion) of participants experiencing any adverse events will be reported.
- h. Eye-level outcomes will be calculated based on the involved eyes for the presenting uveitis. Therefore, bilateral uveitis presentations will be counted as two eyes.
- i. A *p*-value of less than 0.05 will be considered statistically significant.
- j. All statistical analyses will be performed using IBM SPSS Statistics version 28.0.1.0 (142) for Windows (SPSS Inc.).

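### A fixed 0.1 cut in decimal Snellen means that an eye starting at 0.1 or worse can never be classed as decreased, and gains of less than 0.1 from very poor vision are classed as stable

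*Supplement*

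**What the plan says.** SAP v2.0, section 5e under Ocular-level outcomes, bases the outcome on the difference in "best-corrected visual acuity between month 6 and baseline visits (measured with Snellen, in decimal equivalent"). Acuity is taken to have increased if that difference "was equal to or greater than 0.1, stable if within the range of -0.1 to 0.1, and decreased if less than -0.1". The variable is typed as categorical. Final protocol section 6.2f carries the same rule, including "decreased if less than -0.1".

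Entry criteria admit eyes with very low vision. Final protocol section 3c excludes "Patients with visual acuity less than 1/300 or showing signs of preptisis based on ophthalmological examination and ultrasound of the eye". The protocol summary words the limit differently: "visual acuity less than hand movement with signs of phthisis on ophthalmological examinations and ultrasound". Under either wording, an eye between 1/300 and 0.1 can enter. SAP section 6 plans to describe baseline acuity as "Snellen/LogMAR visual acuity, and categorical data: mild visual impairment, moderate visual impairment, severe visual impairment, and blindness", so poor baseline vision is foreseen and logMAR is already named, though only for baseline.

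SAP section 14h states that "Eye-level outcomes will be calculated based on the involved eyes for the presenting uveitis", with bilateral cases counted as two eyes. Section 14 adds no logMAR or continuous analysis of acuity change. Neither document gives a low-vision rule or a code for vision below the chart.

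**The concern.** Decimal acuity has a floor at 0, and equal decimal steps are not equal visual steps. A single absolute cut therefore means something different at each baseline. At the bottom of the scale, no room is left for a fall that would count. Higher up, a modest change is enough to move an eye into another class.

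Visual acuity change is a named secondary outcome in both documents. Among eyes that start at 0.1 or worse, further loss is reported as stable, so a difference between arms in that loss would not appear in the class counts. Gains in those eyes are recognised only once they reach 0.1 decimal, however large they are on a proportional scale. The classes also overlap at one boundary, so some eyes have no unique class.

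**Working it through.** The plan states no figure to reproduce here, so the check applies the written rule to pairs of acuities.

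**Inputs**
- Rule (SAP 5e, protocol 6.2f), with d = month-6 decimal minus baseline decimal: increased if d ≥ 0.1; stable if -0.1 ≤ d ≤ 0.1; decreased if d < -0.1.
- Lowest acuity not excluded by protocol section 3c: 1/300 = 0.0033.
- Assumption: no sight is coded 0. The documents give no code. For an eye starting at 0.1, any code from 0 to 0.0033 gives d between -0.1 and -0.097, which is the same class.
- Proportional size of a change: gain in logMAR units = log10(month-6 / baseline); a negative value is a loss.

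**Floor**

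If baseline b ≤ 0.1 and month-6 acuity is at least 0, then d ≥ 0 - b ≥ -0.1. The decreased class needs d < -0.1, so it cannot be reached. The lower end of the stable range includes -0.1 itself, so even 0.1 to 0 is stable.

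**Rule applied to examples**

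| Baseline | Month 6 | d | Class | Gain, logMAR |
|---|---|---|---|---|
| 0.1 | 0 (assumed) | -0.100 | stable | undefined |
| 0.1 | 1/300 | -0.097 | stable | -1.48 |
| 0.05 | 0 (assumed) | -0.050 | stable | undefined |
| 0.11 | 0 (assumed) | -0.110 | decreased | undefined |
| 1/300 | 0.1 | +0.097 | stable | +1.48 |
| 1/60 | 0.1 | +0.083 | stable | +0.78 |
| 0.05 | 0.1 | +0.050 | stable | +0.30 |
| 1/300 | 0.125 | +0.122 | increased | +1.57 |
| 0.8 | 1.0 | +0.200 | increased | +0.10 |
| 1.0 | 0.8 | -0.200 | decreased | -0.10 |
| 0.1 | 0.2 | +0.100 | increased and stable | +0.30 |
| 0.9 | 1.0 | +0.100 | increased and stable | +0.05 |

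The logMAR entries are, for example, log10(0.1 ÷ 1/300) = log10(30) = 1.48, log10(0.1 ÷ 1/60) = log10(6) = 0.78, and log10(1.0 ÷ 0.8) = 0.10.

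**Meaning of a 0.1 decimal gain at different baselines**

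log10((b + 0.1)/b) is 0.301 at b = 0.1, 0.176 at 0.2, 0.079 at 0.5 and 0.046 at 0.9. The threshold is therefore about 6.5 times as demanding at 0.1 as at 0.9 (0.301 / 0.046).

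**The case against.** The strongest reply is that the defect is local. A reader might infer that the rule hides severe visual loss in general. It does not: falls to no sight from 0.5, 0.3 or 0.2 give -0.5, -0.3 and -0.2, all decreased, and even 0.11 to 0 is caught. A reader might also infer that gains in poorly seeing eyes are mostly missed. The rule does not support that either: 1/300 to 0.125 is increased, as is any gain of more than 0.1 from very poor vision. The block on loss is complete for these eyes; the block on gain is only partial.

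The size of the effect on the result is unknown. Planned baseline categories of severe impairment and blindness show that such eyes are expected to be possible, not that they are common. The outcome is secondary and at eye level, protocol section 1.2 words the secondary objectives as exploratory, SAP section 14 names no test for it, and the primary endpoint and sample size do not use it. Raw acuities are collected, so reclassification would remain possible later. Baseline imbalance can shift the counts of any change categories, so that is not a fault peculiar to this scale.

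All of this stands and limits the weight of the point. None of it removes the defect: no provision in either document gives an eye at 0.1 or worse a route to the decreased class. Reclassifying later would mean choosing the scale after the data are known.

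**Conclusion.** The point holds for eyes with baseline decimal acuity of 0.1 or worse. For them, classification as decreased is impossible under the written rule, whatever happens to the eye, and gains below 0.1 decimal are stable even at 0.78 or 1.48 logMAR. Separately, a change of exactly +0.1 belongs to two classes at any baseline.

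The floor result rests only on acuity not being coded below 0. The example of an eye losing all sight also uses the assumed code of 0, though any code up to 0.0033 gives the same class. The effect on the reported result cannot be sized, because the documents do not say how many eyes start at 0.1 or worse. The primary endpoint is untouched. This is a correction worth making to a secondary outcome, not a threat to the trial's main conclusion.

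**What to change.** In SAP section 5e and protocol section 6.2f:

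1. Convert every acuity to logMAR, and list in advance the values to be used for off-chart vision (counting fingers, hand movement, light perception, no light perception).
2. Define improved, stable and worsened by one prespecified logMAR change, worded so that each value falls in exactly one class. The sponsor should choose the cut. As an illustration only, at 0.2 logMAR a fall from 0.1 to 1/300 (1.48) would be worsened, a rise from 1/60 to 0.1 (0.78) improved, and 0.8 to 1.0 (0.10) stable.
3. Optionally, add a baseline-adjusted comparison of month-6 logMAR as a supportive analysis. The defect does not require this to become the main acuity result, and the conventional off-chart values could weigh heavily in a mean.

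The cost is wording in two places and simple arithmetic on data already collected. The downside is that off-chart values rest on convention; fixing them before analysis is still better than leaving them unstated, as now.
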